## Abstract

**Background:**

In the past 30 years karyotyping was the gold standard for prenatal diagnosis of chromosomal aberrations in the fetus. Traditional karyotyping (TKT) has a high accuracy and reliability. However, it is labor intensive, the results take 14–21 days, the costs are high and unwanted findings such as abnormalities with unknown clinical relevance are not uncommon. These disadvantages challenged the practice of karyotyping. Multiplex ligation-dependent probe amplification (MLPA) is a new molecular genetic technique in prenatal diagnosis. Previous preclinical evidence suggests equivalence of MLPA and traditional karyotyping (TKT) regarding test performance.

**Methods/Design:**

The proposed study is a multicentre diagnostic substitute study among pregnant women, who choose to have amniocentesis for the indication advanced maternal age and/or increased risk following prenatal screening test. In all subjects, both MLPA and karyotyping will be performed on the amniotic fluid sample. The primary outcome is diagnostic accuracy. Secondary outcomes will be maternal quality of life, women's preferences and costs. Analysis will be intention to treat and per protocol analysis. Quality of life analysis will be carried out within the study population. The study aims to include 4500 women.

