### Outcome measures

Primary outcome is diagnostic accuracy. Sensitivity, specificity and failure rates of MLPA are calculated for (an)euploidies 21, 13, 18, X and Y and compared with TKT as a reference test. Turnaround time on laboratory and patient level is recorded. Discordant test results and technical difficulties are counted, allowing for general and per centre analysis. The effect of a learning curve if present will be established.

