### Statistical issues

#### Sample size

Adopting the results of karyotyping as the gold standard and assuming that MLPA and karyotyping do not produce different test results, that not more than 1/500 missed cases of Down syndrome are accepted, and that the proportion of discordant test results is 0.002, we need at least 4500 paired test results to test the null-hypothesis of clinical equivalence (one-sided alpha 0.05, power = 1-beta = 0.90).

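### The stated minimum of 4500 pairs equals the recruitment target of 4500 women, so any failed test leaves fewer pairs than the protocol says it needs; the effect on power is small

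*Protocol article*

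**What the plan says.** In the protocol article, the abstract (Methods/Design) sets recruitment: "The study aims to include 4500 women". It adds that both tests are done on the amniotic fluid of every participant, so one woman normally supplies one pair.

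The Sample size section sets the requirement in pairs: "we need at least 4500 paired test results". The conditions are "assuming that MLPA and karyotyping do not produce different test results", "not more than 1/500 missed cases of Down syndrome are accepted" and "the proportion of discordant test results is 0.002", with "one-sided alpha 0.05, power = 1-beta = 0.90". No test statistic or formula is named, and 4500 is not described as including an allowance for unusable samples.

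Under Outcome measures, failures belong to the primary outcome: "Sensitivity, specificity and failure rates of MLPA are calculated". That section also counts technical difficulties. The Karyotyping subsection says that cells must be cultured before they can be analysed, which is a second way for a result to be missing.

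**The concern.** The requirement is a floor expressed in pairs. The recruitment target is expressed in women and is the same number. The two agree only if no MLPA and no culture fails, yet the protocol plans to measure failures. As printed, the plan reaches its own floor only in the best case.

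The stated 90% power for the primary outcome is attached to 4500 pairs. A reader cannot tell whether 4500 is the raw requirement, in which case losses come off it, or an already inflated one, in which case the wording of a minimum number of pairs is wrong.

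**Working it through.** **Inputs from the Sample size section**
- One-sided alpha 0.05, z = 1.645; power 0.90, z = 1.282.
- Discordant proportion ψ = 0.002.
- True difference 0, so 0.001 in each direction.
- Margin δ = 1/500 = 0.002. Reading the limit on missed cases as a margin on the paired difference is an interpretation.

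**Input from the abstract:** 4500 women, one pair each.

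**Assumption, not in the document:** combined failure rate f of 1%, 3% or 5%, where a pair is lost if either test fails.

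**Step 1: the plan's own figure.** The Wald formula for a paired difference is

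n = (z_α + z_β)² ψ / δ² = (1.645 + 1.282)² × 0.002 / 0.002² ≈ 4282 (computed with unrounded z).

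This is 218 below 4500 (218/4500 = 4.8%), so 4500 is not reproduced exactly. Other standard choices do not give it either:
- Wald with two-sided alpha: 5254.
- Wald with power 0.80: 3092.
- Wald with a continuity correction of 0.5/n or 1/n: 4769 or 5235.
- Score test with restricted estimates: 5686.

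The printed 4500 could be 4282 rounded up, or 4282/0.95 = 4508 rounded down. The article states neither.

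**Step 2: pairs left from 4500 women,** 4500 × (1 − f):
- 1%: 4500 × 0.99 = 4455
- 3%: 4500 × 0.97 = 4365
- 5%: 4500 × 0.95 = 4275

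**Step 3: power on the Wald formula,** Φ(δ√(n/ψ) − 1.645). At n = 4500 the first term is 0.002 × √(4500/0.002) = 3.000, so power is Φ(1.355) = 91.2%.

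**Step 4: power without the normal approximation.** The expected number of discordant pairs is 4500 × 0.002 = 9, which is few for a normal approximation. I took the two discordant counts as Poisson, with rate 0.001 in each direction under the plan's assumption and rates q + 0.002 and q under the null. For each q, the most powerful 5% test (Neyman–Pearson) was found. The smallest of these powers over q is a ceiling for any test that holds 5% whatever the discordance rate.

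| Failure rate (assumed) | Pairs | Wald power | Ceiling for a test holding 5% |
|---|---|---|---|
| 0% | 4500 | 91.2% | 85.9% |
| 1% | 4455 | 91.0% | 85.7% |
| 3% | 4365 | 90.5% | 84.9% |
| 5% | 4275 | 90.0% | 84.2% |

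**Step 5: separate the causes.** Reading down each column, losses cost about 0.2, 0.7 and 1.3 points on the Wald formula and about 0.3, 1.0 and 1.7 points on the ceiling (differences of unrounded values). The step from 90% to 85.9% is already in the first row, where nothing has failed. It comes from the normal approximation with about 9 discordant pairs.

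**The case against.** A reader might infer that failed tests pull the trial from 90% down to 84–86%. The document does not support that. Step 5 shows that about 4 of those points are there with no losses at all, and they concern the choice of power method, which is a separate matter. The ceiling also carries a condition that the protocol does not impose: the test must hold 5% at every discordance rate. The least favourable null has q of about 0.00055, hence total discordance of 2 × 0.00055 + 0.002 ≈ 0.003, not the 0.002 that the plan assumes.

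A reader might also infer that 4500 certainly contains no reserve. That is not established either. On the Wald formula there are 218 pairs to spare, and 90% survives losses up to about 4.8%. But 4282 is not in the article and no method is named, so the reserve is conjecture too, and the continuity-corrected and score sizes (4769 to 5686) leave none.

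Three further objections are fair. The recruitment figure is an aim, not a cap. Multiple pregnancies are not excluded and could add samples. The article does not say how a failed test enters the intention-to-treat and per-protocol analyses, so not every failure need remove a pair from every analysis. An allowance may also stand in the full protocol, which is not shown.

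What remains is narrower than a complaint about missing detail: two printed numbers in different units are treated as equal, and one of them is called a minimum.

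**Conclusion.** The mismatch is real as printed: 4500 women with one pair each give 4500 pairs only if nothing fails, and the protocol itself measures failures. Its consequence is minor. At assumed combined failure rates of 1% to 5% the trial would have 45 to 225 pairs fewer than stated, and power would fall by about 0.2 to 1.3 points on the Wald formula or 0.3 to 1.7 points on the stricter ceiling. This rests on the assumed failure rates, on 1/500 being the margin for the paired difference, and on each failure costing a pair. It does not show that failures leave the trial materially underpowered, or that the recruitment target has to rise.

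**What to change.** Keep 4500 women. In the Sample size section, replace the phrase "we need at least 4500 paired test results" with the number of evaluable pairs expected from 4500 women after an explicit combined MLPA and culture failure rate, labelled as an assumption (for example, 4365 pairs at 3%). Give the power at that number and name the test it refers to, since the answer at 4365 pairs is 90.5% on the Wald formula but at most 84.9% for a test that holds 5% over all discordance rates.

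If 4500 already includes an allowance, say so instead, and print the uninflated minimum (4282 on the Wald formula) with the failure rate used.

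Either way the change is a sentence or two, with no extra enrolment and no change of design. The cost is a slightly less favourable printed number. Holding to 4500 evaluable pairs would instead mean 4500/(1 − f) women, that is 4546, 4640 or 4737 at 1%, 3% or 5%. An effect of this size does not call for that.

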**Discussion:**

The study results are expected to help decide whether MLPA can replace traditional karyotyping for 'low-risk' pregnancies in terms of diagnostic accuracy, quality of life and women's preferences. This will be the first clinical study to report on all relevant aspects of the potential replacement.

**Trial Registration:**

The protocol is registered in the clinical trial register number ISRCTN47252164

## Background

In the Netherlands, invasive prenatal diagnosis is offered to all women who are considered to be at increased risk for Down's syndrome. Until recently, the vast majority of invasive tests was done for advanced maternal age. More recently, a nationwide screening program for Down's syndrome using first trimester serum testing combined with ultrasonographic nuchal translucency measurement was introduced [1,2]. A positive result of this combination test or maternal age (36 years or older) represent 80% of the indications for the invasive diagnostic procedures (amniocentesis and chorionic villus sampling). We have seen a still continuing shift of maternal age-based karyotyping towards prenatal screening based testing.

Traditional karyotyping (TKT) is considered the gold standard for invasive prenatal diagnosis (PND) [2,3]. TKT is able to detect a range of numerical and structural chromosomal abnormalities with considerable accuracy (99.4–99.8%) and reliability[3,4]. However, TKT also has several disadvantages: it is labour intensive and the costs are high. Furthermore, obtaining results from karyotyping takes 2–3 weeks, and this waiting time places a significant emotional burden on women and their partners[5]. Moreover, the extensive detection capacity of TKT can be perceived as a disadvantage due to the detection of abnormalities with unclear or mild clinical relevance. These results can cause patient anxiety, emotional dilemmas concerning the continuation of pregnancy and, albeit rare, unnecessary pregnancy terminations [6].

Due to these disadvantages, TKT has been challenged as a reference test. In 2002, a molecular PCR-based technique, MLPA (multiplex ligation-dependent probe amplification) became available to detect foetal aneuploidies in amniotic fluid cells. In preclinical laboratory studies, MLPA has been a robust test in detecting the most common chromosomal aneuploidies, namely trisomy 21, 13, 18 and sex chromosome abnormalities [7-9]. Compared to TKT, MLPA has several potential advantages: the result is available in 2–4 days instead of 3 weeks, the technique requires only 2 ml of amniotic fluid instead of 16–20 ml, and the technique is considerably less labour-intensive and is suitable for high-throughput testing [8-10].

In the Netherlands, like other western countries, there is an ongoing debate whether rapid molecular tests should be used as a stand-alone diagnostic tool instead of karyotyping in prenatal diagnosis for certain indications[5,11-15]. To strengthen the debate and to supply it with evidence, we designed a clinical prospective cohort study in which MLPA is compared independently to TKT for the two main referral indications; advanced maternal age and increased risk following prenatal screening tests. The aim is to estimate diagnostic accuracy for the detection of trisomies 21, 18,13 and sex chromosome abnormalities, as well as the reduction in waiting time for the prospective parents, maternal quality of life, women's preferences, the relevance of 'unexpected findings' and costs.

## Methods/Design

### Aims

The M.A.K.E. study investigates whether MLPA can replace TKT in prenatal diagnosis in terms of diagnostic accuracy, costs and maternal quality of life for women undergoing amniocentesis for the indications advanced maternal age and increased risk following prenatal screening.

We hypothesize that MLPA has equivalent diagnostic accuracy in detecting trisomies 21, 18, 13 and sex chromosome abnormalities. The reduction in waiting time for the patient, maternal quality of life, women's preferences, the relevance of 'unexpected findings' and costs are part of the study.

### Study design

The M.A.K.E. study is a prospective, nationwide multicenter study. All eight genetic centres in the Netherlands will participate.

### Participants

Participants are pregnant women choosing to have amniocentesis for either advanced maternal age or increased risk following prenatal screening.

Women undergoing amniocentesis for ultrasound abnormalities, parental chromosomal abnormality, or a previous child with chromosomal abnormality are excluded.

### Procedures, recruitment and collection of baseline data

Pregnant women who visit one of the participating antenatal care units are informed by an obstetrician, midwife or genetic counsellor on the different test strategies (prenatal screening and prenatal diagnosis) with associated risks and benefits of each procedure. After they have chosen to have amniocentesis, eligible women will receive participation information. After written consent, amniotic fluid is obtained and tested with both MLPA and karyotyping. Stratification will be applied for each centre. Baseline demographic characteristics and obstetric history are recorded. For the quality of life study and women's preference study a representative sub sample is drawn, with separate consent procedure.

### Diagnostic tests

Details on amniocentesis are recorded in the case record form, accessible through a secure website [16]. All amniotic fluid samples are tested with both MLPA and TKT. Test results are blindly assessed. We chose not to fully standardize the MLPA and TKT protocols but to accept the minor differences within the eight laboratories in sample preparation, formulation of the trisomy multiplex, equipment and interpretation of results. This will make the trial more pragmatic, with better generalizability of the results. The existing differences will be administered and will be helpful in choosing the best test strategy in the nearby future.

#### MLPA

In this study we use a commercially available kit, SALSA MLPA P095 (MRC Holland, the Netherlands). For each specific genomic target, a set of 2 probes is designed to hybridize immediately adjacent to each other on the same target strand. Both probes consist of a short target specific sequence and a universal PCR primer-binding site. One of the probes contains a so called 'stuffer sequence'. For each probe in the multiplex, the stuffer part has a specific length and sequence. After overnight hybridization to the target DNA, each pair of adjacent probes is joined by a ligation reaction. Next, PCR is performed with a single fluorescent-labelled primer pair, which ensures that the relative yield of each of the PCR products is proportional to the amount of each of the target sequences. The different length products are separated on an automated capillary sequencer and the peak areas are quantified[9].

Compared to other techniques available for rapid aneuploidy detection (RAD), i.e. quantitative fluorescence polymerase chain reaction (QF-PCR) and fluorescence in situ hybridization (FISH), MLPA has the advantage of detecting 40 different loci in a single reaction. Furthermore, MLPA is suitable to tailor-made strategies for different clinical settings. Compared to FISH, MLPA is suitable for high-throughput testing and less expensive. Compared to QF-PCR, MLPA avoids the problem of non-informativeness of the polymorphic markers that may occur with QF-PCR [17]. However, in contrast to QF-PCR, MLPA will not diagnose 69, XXX triploidy.

#### Karyotyping

Karyotyping is a reliable and accurate test for detecting chromosomal aberrations. The karyotyping detection rate for Down syndrome is 99,5% [3].

The time from amniocentesis to diagnosis is 2–3 weeks, as the test is non-automated and samples need to be cultured in order to obtain foetal cells at the metaphase stage. Laboratory personnel involved in TKT are blinded for MLPA results. In case of an abnormal MLPA result and a more rapid test result is wanted, the earliest possible harvesting of cell cultures is carried out.

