#### Data analysis

Data will be analyzed according to both the intention to treat and per protocol analysis. To determine non-inferiority in diagnostic accuracy we will calculate absolute and relative sensitivity, specificity and failure numbers of MLPA and compare these to karyotyping (gold standard). Furthermore, the time cytogeneticists or molecular geneticists need to provide an authorized test results and the time needed to inform the patients is recorded. With these data exact waiting periods for both tests can be estimated.

Quality of life outcomes. Repeated measurement analysis will be performed for the between group evaluation.

Women's preferences. Responses on the discrete choice experiment will be analyzed using conditional logistic regression techniques.

Economic evaluation. Since the study is designed as an equivalence study, we hypothesize there is no difference in diagnostic accuracy between MLPA and TKT. The economic analysis is expected to be a cost-effectiveness analysis with maternal health as effectiveness.

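### Early culture harvest prompted by an abnormal MLPA result is an unacknowledged exception to the stated blinding of karyotyping, and it makes the TKT time in those samples depend on MLPA

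*Protocol article*

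**What the plan says.** On blinding, the Diagnostic tests section says "Test results are blindly assessed". The Karyotyping section is more specific: "Laboratory personnel involved in TKT are blinded for MLPA results". Neither statement carries an exception.

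The sentence that follows the second statement reads: "In case of an abnormal MLPA result and a more rapid test result is wanted, the earliest possible harvesting of cell cultures" is carried out. No other trigger for early harvest is named. No intermediary or separate harvesting team is described.

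TKT is the reference test for the primary outcome. The Outcome measures section lists sensitivity, specificity and failure rates of MLPA against TKT, together with a count of discordant results.

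On time, the same section says "Turnaround time on laboratory and patient level is recorded", and the Data analysis section adds "With these data exact waiting periods for both tests can be estimated". Reduction in waiting time is also part of the study under Aims.

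**The concern.** The two adjacent sentences under Karyotyping cannot both hold without qualification. If cultures are harvested early because MLPA was abnormal, whoever receives that request in the TKT laboratory can infer the MLPA result.

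Two things are at stake.

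- **Independence of the reference reading.** A reader who knows that MLPA was abnormal may resolve an equivocal karyotype, such as a mosaic or borderline sample, toward MLPA. An apparent false positive would then be counted as a true positive. The exposure is selective, because only MLPA-abnormal samples can be affected.
- **Meaning of the TKT waiting time.** In an early-harvested sample the TKT time is partly a consequence of MLPA. It does not show how long the woman would have waited with karyotyping alone, which is the comparison needed when asking whether one test can replace the other.

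**Working it through.** The protocol article gives no figure for this point, so there is nothing of its own to reproduce. The check has three steps.

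**1. Which samples are exposed**

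| MLPA | TKT | Can early harvest be triggered? |
|---|---|---|
| abnormal | abnormal (true positive) | yes, if speed is wanted |
| abnormal | normal (false positive) | yes, if speed is wanted |
| normal | abnormal (false negative) | no |
| normal | normal (true negative) | no |

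Both conditions must be met: an abnormal MLPA result and a wish for a faster result. The missed Down syndrome cases that the Sample size section uses as its limit (1/500) lie in the third row and are not exposed.

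**2. Size for diagnostic accuracy**

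The documents do not say how many results will be abnormal. Assumed counts for illustration among 4500 samples: 90 true positives, 1 false negative and 2 false positives. Suppose both false positives are read toward agreement.

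- Sensitivity = TP/(TP + FN): 90/91 = 98.90% becomes 92/93 = 98.92%, a change of 0.02 percentage points.
- Specificity: 2 of about 4400 normal samples is about 0.05 percentage points.
- Discordance count: the Sample size section assumes a discordant proportion of 0.002, so 4500 × 0.002 = 9. Each call shifted to agreement removes one from the false-positive part of that count. The split of the 9 between false positives and false negatives is not given.

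**3. Size for waiting time**

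Inputs from the documents:
- TKT takes 2–3 weeks (Karyotyping: "The time from amniocentesis to diagnosis is 2–3 weeks, as the test is non-automated and samples need to be cultured"), midpoint 17.5 days.
- MLPA takes 2–4 days (Background: "the result is available in 2–4 days instead of 3 weeks"), midpoint 3 days.
- Unaffected gap = 17.5 − 3 = 14.5 days.

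Assumed, because the documents do not give them: proportion abnormal p = 1–5%; share of these harvested early r = 50–100%; days saved s = 3–7.

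- Samples affected = 4500 × p × r: from 4500 × 0.01 × 0.5 (about 22) to 4500 × 0.05 × 1 = 225.
- Overall mean gap = 14.5 − p × r × s: from 14.5 − 0.01 × 0.5 × 3 = 14.485 to 14.5 − 0.05 × 1 × 7 = 14.15 days, a fall of 0.1% to 2.4%.
- Mean gap in MLPA-abnormal women = 14.5 − r × s: from 14.5 − 0.5 × 3 = 13.0 to 14.5 − 1 × 7 = 7.5 days, a fall of 10% to 48%.

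**The case against.** The strongest reply has four parts.

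- **Disclosure is inferred.** The article speaks of harvesting cultures. It does not say that those who harvest also read the karyotype, or what they are told. Routing of requests is the kind of detail a condensed article leaves to the full protocol. This stands in part: disclosure to the reader is an inference. But the blinding statement covers all personnel involved in TKT, not only the reader, and harvesting is TKT work. The statement therefore needs qualifying whatever the routing is.
- **The trial's critical error is untouched.** This stands. Missed cases never trigger early harvest. A reader might infer that all MLPA-positive samples are unblinded and that sensitivity is therefore compromised. The documents do not support that: a wish for speed is also required, and sensitivity depends on false negatives as well. Nor can one or two shifted calls be presented as 11–22% (1/9 to 2/9) of a count wholly open to the bias, since only its false-positive part is exposed.
- **Waiting time is barely affected, and the bias runs against MLPA.** This stands for the overall mean. It does not stand for women with abnormal results. Separate reporting could well be set out in an analysis plan that is not shown, so its absence is not an error. What needs correcting is the unqualified promise of exact waiting periods for both tests.
- **Quality of life.** A reader might infer that early harvest shortens the wait in the comparison group that receives only the TKT result. The Secondary outcomes section does not say whether early harvest is requested for women who are not given an MLPA result, so this remains conditional.

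**Conclusion.** The point holds within limits. As written, blinding without exception is not a property the design has for MLPA-abnormal samples harvested early, and their TKT times are not times under TKT alone.

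For accuracy, the exposure is mainly apparent false positives, specificity and the discordance count. In the illustration the change is about 0.05 percentage points in specificity and 0.02 in sensitivity, so what is chiefly at risk is the claim of an independent reference reading. For waiting time, the effect on the overall mean is negligible (at most 2.4% under the assumed ranges). Among MLPA-abnormal women the time saved by MLPA is understated by 10% to 48% under the same ranges.

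These sizes rest on assumed values for the abnormal proportion, the uptake of early harvest, the days saved and the illustrative counts. That the sentences conflict does not depend on any of them. Nothing here bears on whether early harvest is clinically appropriate.

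**What to change.** Reconcile the Diagnostic tests and Karyotyping statements without changing when early harvest is offered:

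1. Either state that blinding is partial for early-harvested samples, or have the karyotype read and recorded for chromosomes 13, 18, 21, X and Y by existing staff who are told neither of the early-harvest request nor of the MLPA result. Merely leaving the MLPA result off the request is not enough: with no other trigger named, the request itself gives it away.
2. Record early harvest in the case record form.
3. Report concordance separately for early-harvested samples.
4. Report TKT turnaround with and without these samples. Do not censor them at early harvest: harvest depends on the MLPA result, so that censoring would be informative.

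The cost is one case-record field, a short laboratory instruction and a few extra lines of analysis.
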